#### **4.5.5. Randomisation**

##### **4.5.5.1. Randomisation practicalities**

Randomisation will be performed using a random number generated as implemented in the statistical computing environment R. Randomisation will be by permuted blocks (random block sizes of 7 or 14 participants) to guard against bias introduced over time, such as outbreaks of pathogenic bacteria in the hospital. Participants will be randomised 1:1:1:1:1:1 to the 6 treatment and 1 control arms.

Randomisation will be built into electronic data systems using algorithms developed by the data management team at the Malawi Liverpool Wellcome Trust (MLW). The participant's trial number, treatment allocation and the date of randomisation will be entered into the trial register at the site.

##### **4.5.5.2. Randomisation codes and unblinding**

The allocation will not be blinded as this is not practical given the number of factors evaluated. However, the primary end point (total bacterial load in colony forming units (CFUs)) is quantitative in nature and will be assessed by laboratory staff blinded to randomisation. See [Section 10.1.1](#) for further information.

##### **4.5.5.3. Co-enrolment guidelines and reporting**

Co-enrolment in another interventional trial is not permitted for the duration of follow-up. Co-enrolment in other non-interventional (i.e. observational) studies may be allowed but should be discussed with the trial management group before enrolment.

#### **4.6. Treatment of patients**

##### **4.6.1. Introduction**

All women and neonates will receive routine hospital care as laid out in local policies and guidelines for all procedures, except for the interventions of the trial including antiseptic application and the trial's clinical and microbiological assessments. Labouring women and neonates will be randomised into one of the 7 arms of the trial 1:1:1:1:1:1:1 as follows:

#### **Figure 3: Trial arms**

[figure not shown]

**4.6.2. Trial treatments**

At the point of recruitment baseline clinical and demographic data will be collected for all participants, and a baseline skin assessment performed and documented.

Participants in both strata, other than those randomised to the control group, will be randomised to either 1% CHG, 2% CHG or Octenidine dihydrochloride 0.1% phenoxyethanol 2% (OHP, trade name Octenisept®), at different frequencies ([see above](#)). Each application will be recorded in the appropriate CRF.

**4.6.2.1. Justification for Choice of Intervention**

**4.6.2.1.1. Maternal strata**

CHG is the most widely used antiseptic in labour and is on the WHO list of essential medicines(31). One percent CHG was well tolerated in labouring women from Zimbabwe(32,33), however, two

applications were required to achieve an ~80% reduction in bacterial load. This study will test CHG in concentrations up to 2% to determine if increasing concentration of CHG leads to increased efficacy. Concentrations will be limited to 2% because of a rare case report of mucosal damage with higher concentrations(34).

There is good data on safety and tolerability of OCT 0.1% (35,36) and OHP in female populations(18,37,38) and some evidence that OCT (and OHP) has improved action against gram negative organisms compared to CHG, particularly in the presence of organic material. We have elected to test the standard available preparation of 0.1% octenidine with 2% phenoxyethanol (OHP).

Antiseptic application in labour is invasive and requires personnel; interventions must therefore be limited to the minimum necessary to achieve adequate reductions in bacterial load. However, there is some evidence that more than one intervention may be required for optimum effect (see above). We therefore plan to compare a single vaginal cleansing intervention with 4 hourly repeat interventions up to a maximum of 6 applications, a frequency well tolerated by labouring women in Zimbabwe and consistent with WHO recommendations for frequency of vaginal examination during labour(33,39). A control arm receiving standard of care will also be recruited.

#### **4.6.2.1.2. Neonatal strata**

CHG is used in neonatal units (NNUs) in concentrations from 0.2-4%(40–43). Previous large- scale studies of CHG to decolonise neonatal skin have used concentrations towards the lower end of the range(22); however babies born in LMIC with high levels of environmental contamination may require relatively high concentrations to achieve effective decolonisation. This study will use an upper limit of 2% CHG because of rare reports of skin damage with concentrations of CHG  $\geq 2\%$ , although these are mostly limited to infants <1000g at birth(44). This trial is only recruiting neonates with a birth weight >1000g. OCT 0.1% and 0.1% Octenidine 2% Phenoxyethanol (OHP) are the standard antiseptics in neonatal unit's in Germany and there are published data on safety in neonates(16), including premature newborns(45). This study of OHP in premature newborns also demonstrated that although phenoxyethanol undergoes cutaneous absorption, it almost completely metabolizes to 2-phenoxyacetic acid, which can be detected in the urine. As with the maternal strata, OHP will be tested at a single concentration because of limited published data.

Previous studies from high income countries have documented a significant decline in skin bacterial load for up to 48 hours following a single topical application of CHG(14), however infants from LMIC may be exposed to high levels of environmental contamination during birth and in the postnatal period. This study will therefore compare a single antiseptic application to 24 hourly repeat applications until discharge, up to a maximum of 72 hours. Twenty-four hourly applications were selected as the maximum feasible to scale up in a LMIC setting. A control arm receiving standard of care will also be recruited.

#### **4.6.2.2. Maternal treatment**

The antiseptic will be applied to the vagina and perineum. Participants will receive the intervention according to the frequency schedule they were assigned to (either single application or 4 hourly [during working hours, up to 6 applications]), aligned with routine maternal vaginal examinations.

Further details can be found in the MOP.

Before an antiseptic is applied or swabs are taken, a toxicity assessment will be performed (see [Appendix II](#)). This will assess for vaginal/vulval irritation, erythema, skin breakdown and swelling (more details in [Section 4.7.3](#)).

The normal bathing and washing regime will be permitted.

#### **4.6.2.3. Neonatal treatment**

The antiseptic will be applied topically to the whole body with the same volume of CHG/OHP, excluding the face to avoid the eyes.

Before an antiseptic is applied, the neonate's temperature will be measured and the skin condition score assessment will be performed. Whilst treatment is being applied, precautions should be taken to keep the baby warm and also to avoid pooling of the antiseptic around the baby. After the application, the neonate should be re-dressed and their body temperature will be measured after 15 minutes. The neonate should be observed for skin reactions at 30 minutes after each application.

In the case of rare and highly unlikely accidents such as splash injury to the eye from antiseptic, flush the affected area with copious saline as quickly as possible and inform the local paediatric services. See MOP for further details.

The normal bathing, washing and cord care regime delivered by the nursing staff or family will be permitted.

#### **4.6.2.4. Dispensing**

Antiseptic will be transported to the ward in pre-defined concentrations. Containers for individual use will be prepared on the ward and labelled for clinical trial use, adding the trial number to each container immediately after randomisation. These containers should not be shared with any other trial participants or patients outside the trial. Further details will be provided in the Manual of Procedures (MOP).

#### **4.6.2.5. Dose interruptions and discontinuations**

Doses and concentrations will not be modified after the participant has been randomised. Consideration of temporary or permanent discontinuation of antiseptic use should be made at the discretion of the treating clinician in the following circumstances:

Mothers:

- Concerns over perineal skin/vaginal mucous membrane integrity: score  $\geq 3$  in any category immediately before antiseptic application or  $>2$  in 2 or more categories (see [Appendix II](#))
- Any reason or change in clinical condition the treating clinician deems antiseptic application is not appropriate (i.e. antepartum haemorrhage)

Neonates:

- Hypothermia  $< 36.0^{\circ}\text{C}$  immediately before antiseptic application
- Skin score  $>2$  in any category immediately before antiseptic application (see [Appendix I](#))
- Neurological disturbance

When antiseptic is temporarily stopped for any reason, an assessment will be performed at the time of the next scheduled application and the clinician will determine whether it should be re-started. Treatment

interruptions and discontinuation and the reason for this should be recorded as appropriate on the trial CRFs.

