#### **4.6.2.6. Stopping CHG/OHP early (permanent discontinuation)**

Stopping antiseptic permanently before the 6th application or birth (mothers) or discharge/72 hours (neonates) will be decided by the clinician. Possible reasons for permanent discontinuation would include relevant change in maternal or neonatal condition as decided by the clinician, or significant toxicity possibly related to the IMP as identified by the vaginal toxicity assessment and the neonatal skin score. Standard of care will then be delivered as decided by the local clinician.

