### 6.2. Ethical conduct

#### 6.2.1. Ethical considerations

By necessity this trial recruits potentially vulnerable groups (labouring women, neonates). Every care will be taken to respect women and newborns at this time and to ensure that recruitment and participation does not interfere with clinical care.

The autonomy of women and parents/carer's will be protected throughout the trial and during the informed consent process. Risk of coercion will be reduced by separating the role of the clinical team and the researchers, with the clinical team acting as advocates for their patients. Care will be taken to gain and record written informed consent at an appropriate time before enrolment. Before consent is obtained, women and parents/carers will be fully informed of known risks and possible benefits by a participant information leaflet, and this will be reinforced by discussions with the trial research team. Additionally, the woman and their partner will have opportunity to discuss the study and have any questions answered. Women who are already known to be in active labour will not be approached by the research midwife, and will not be eligible for inclusion. Further information is in Section 4.5.3 ([Section 4.5.3](#)).

Antiseptic and swabs will be administered by trial staff at the time of planned vaginal examinations to minimise interruption to clinical care. Condition of the external mucous membranes will be examined prior to administration and antiseptic will not be applied if they are damaged or inflamed or if the participant has reported any severe side effects.

One ethical concern in this trial relates to potential skin or mucous membrane damage. Antiseptics, including CHG and OHP, are widely used for skin disinfection in neonates and mothers and are typically well tolerated. The main risk is with high concentrations (>2%) in extremely low birth weight/preterm neonates (<1kg/<28 weeks), among whom skin reactions have been observed, particularly when chlorhexidine is combined with alcohol. Hypothermia has also been observed after skin cleansing with chlorhexidine on the first day of life. This trial will exclude neonates less than 1kg at enrolment which will minimise, although not entirely eradicate these risks. However, close and regular monitoring of the

skin with a standardised skin condition scoring system, and temperature checking after application will allow chlorhexidine to be discontinued at the discretion of the local clinician.

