### **4.8. Secondary safety outcome analyses: skin score**

A summary table will be presented:

- Skin score at baseline: mean (SD) [N]
- Skin score at each assessment time point: mean (SD) [N]
- Change in total log10 CFU from baseline to each assessment time point: mean (SD) [N]

- Absolute skin score at baseline: n(%) 0, 1, 2...
- Absolute skin score at each assessment time point: n(%) 0, 1, 2...

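### Protocol 4.6.2.5 leaves withholding antiseptic from mothers to clinician discretion at a score threshold, while 6.2.1 makes it mandatory without one, and nothing says which governs

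*Protocol*

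**What the plan says.** Three places in the protocol govern when a mother does not receive a scheduled application.

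- **Section 4.6.2.5** introduces its list with "Consideration of temporary or permanent discontinuation of antiseptic use should be made at the discretion of the treating clinician in the following circumstances". The first maternal item is headed "Concerns over perineal skin/vaginal mucous membrane integrity: score" and gives two criteria joined by *or*: 3 or more "in any category immediately before antiseptic application or" above 2 "in 2 or more categories". The second maternal item is open-ended and covers any reason or clinical change for which the clinician judges application inappropriate.
- **Section 4.6.2.6** leaves permanent stopping to the clinician. Among the possible reasons it names "significant toxicity possibly related to the IMP as identified by the vaginal toxicity assessment and the neonatal skin score", with no score threshold.
- **Section 6.2.1** says that the external mucous membranes are examined before administration and that "antiseptic will not be applied if they are damaged or inflamed or if the participant has reported any severe side effects".

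The assessment made before each application or swab is described in section 4.6.2.2: "This will assess for vaginal/vulval irritation, erythema, skin breakdown and swelling". The scale is in Appendix II, which is not in the text available for this review.

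**The concern.** Sections 4.6.2.5 and 6.2.1 deal with the same examination at the same moment, yet they differ in two respects. One is status: the first asks the clinician to consider stopping, the second says the product is not applied. The other is threshold: the first works from a score, the second from any damage or inflammation, or any severe reported side effect.

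What is at stake is a safeguard. Evaluating safety is a stated objective (section 3), maternal toxicity is a secondary outcome (section 4.10.2.2), and section 6.2.1 itself treats safety as a main reason for running the pilot. Midwives working from the treatment section could give an application that the ethics section says will not be given. The trial is open label, so two available rules also leave room for uneven practice between arms. That could affect how much antiseptic is received and how the toxicity comparison reads.

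**Working it through.** **1. The rules side by side**

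| Mother's state before an application | 4.6.2.5 | 6.2.1 |
|---|---|---|
| Score of 3 or more, reflecting damage or inflammation | Clinician considers stopping; may continue | Not applied |
| Inflammation or damage present, all scores below 3 | Score criteria not met (for whole-number scores); clinician may still withhold | Not applied |
| Severe side effect reported | No separate criterion; covered only by a score or by the open item | Not applied |
| No damage, inflammation or severe side effect | Score criteria give no reason to withhold | No bar |

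In the first three rows, an application that 4.6.2.5 allows is one that 6.2.1 rules out. Neither section refers to the other, and 4.6.2.6 does not rank them.

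**2. How the score criteria relate to each other**

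Inputs: four categories (irritation, erythema, skin breakdown, swelling; section 4.6.2.2). Criterion A is any score of 3 or more. Criterion B is a score above 2 in at least two categories. *Assumption:* scores are whole numbers. The only indirect support is the planned tabulation "Absolute skin score at baseline: n(%) 0, 1, 2" and so on, in section 4.8 of the analysis plan text that follows the protocol. That line does not define the maternal scale.

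Scale 0 to 3:
- All patterns: 4^4 = 256.
- No score of 3: 3^4 = 81, so A is met in 256 − 81 = 175.
- Exactly one score of 3: 4 × 3^3 = 108, so B is met in 256 − 81 − 108 = 67.
- B met without A: 0.

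Scale 0 to 4:
- All patterns: 5^4 = 625.
- A is met in 625 − 81 = 544.
- B is met in 625 − 81 − (4 × 2 × 27) = 328.
- B met without A: 0.

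For whole numbers, above 2 and 3 or more are the same condition, so every case of B is already a case of A.

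Sensitivity, half-point scale 0 to 3 (7 levels):
- All patterns: 7^4 = 2401.
- B without A needs at least two scores of 2.5 and none of 3: 6^4 − 5^4 − (4 × 5^3) = 1296 − 625 − 500 = 171.

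The redundancy therefore depends on whole-number scoring.

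**3. Room for the two sections to disagree below the threshold**

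On either whole-number scale, 81 − 1 = 80 patterns have at least one non-zero score and meet neither A nor B. Where such a score reflects inflammation or damage, 6.2.1 bars application although the score criteria of 4.6.2.5 are not reached. This counts possible patterns and is not a frequency of patients.

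**4. Upper limit on affected repeat applications**

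- Women in multiple-application arms: 3 × 21 = 63.
- Repeat applications per woman: at most 6 − 1 = 5.
- Ceiling: 63 × 5 = 315.

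**The case against.** The best reply is that both sections can be obeyed at once. The open item in 4.6.2.5 lets the clinician withhold for any reason, so a clinician who follows 6.2.1 never breaches 4.6.2.5. That is true, and it narrows the point: the conflict runs in one direction only. It does not remove it, because permission to withhold is not a duty to withhold, and staff who follow 4.6.2.5 alone may apply what 6.2.1 excludes. Section 6.2.1 does later mention the local clinician's discretion, but that sentence closes a discussion centred on neonatal skin and temperature. If it were read as covering mothers too, 6.2.1 would disagree with itself. The manual of procedures may add detail, but it should not have to choose between two protocol statements.

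Several stronger readings are tempting and are not supported:

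- **That the two-category criterion can never act.** It can be met. At most it adds no case, and only with whole-number scores, which Appendix II would settle. Redundancy alone also causes no confusion: the score rule then reduces to 3 or more in any category, which staff can apply.
- **That the ethics committee relied on 6.2.1.** Section 6.2.2 says only that the protocol and other materials are submitted for approval.
- **That the conflict changes the trial's main result.** The primary analysis is by intention to treat (section 4.10.4) and includes women whatever they received. Secondary analyses will weight for departure from the randomised strategy, but no text makes that status depend on whether withholding was mandatory or discretionary. How to classify withheld applications is a separate question.
- **That first applications add materially to the problem.** Poor perineal and vaginal skin condition is an exclusion (section 4.5.1.2), so few women should be in the disputed state at first application.

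**Conclusion.** The protocol contradicts itself on when antiseptic is withheld from mothers. Sections 4.6.2.5 and 6.2.1 differ in both status and threshold, nothing ranks them, and following the first as written allows applications that the second forbids. This conclusion needs no assumption about the difference in status. The difference in threshold assumes only that inflammation or damage can be scored below 3, which the missing Appendix II would confirm.

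The size is not known. The documents give no expected frequency of mucosal inflammation, damage or severe side effects. The figure of 315 repeat applications is a ceiling that assumes every woman in the multiple-application arms receives all six. Applications stop at birth, and the analysis plan text (section 2.6) expects few women to labour for 32 hours.

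The overlap between the two score criteria is a side note, conditional on whole-number scoring. It is a reason to check the wording and does not show which threshold, if either, was mistyped.

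**What to change.** Reconcile sections 4.6.2.5 and 6.2.1 into one rule for mothers, worded identically in both places, stating whether it is mandatory or discretionary and how it relates to the toxicity score. Check that section 4.6.2.6 agrees with it. The clinical team must choose the rule and the thresholds; this review takes no view on either.

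At the same time, compare the two score criteria with the Appendix II scale and confirm that they are written as intended.

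The cost is a wording amendment to the protocol and a matching note in the manual of procedures. Sample size, randomisation and the primary analysis do not change.

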#### **4.6.2.6. Stopping CHG/OHP early (permanent discontinuation)**

Stopping antiseptic permanently before the 6th application or birth (mothers) or discharge/72 hours (neonates) will be decided by the clinician. Possible reasons for permanent discontinuation would include relevant change in maternal or neonatal condition as decided by the clinician, or significant toxicity possibly related to the IMP as identified by the vaginal toxicity assessment and the neonatal skin score. Standard of care will then be delivered as decided by the local clinician.

#### **4.6.2.7. Handling cases of overdose**

For the purposes of this trial, overdose will be defined as more than 4 hourly in the mothers or more than once daily application in the neonates. Any additional doses given will be recorded on the treatment CRF and an AE form completed. Adverse reactions due to this would be expected to be similar to those described in [Section 4.7.3](#) and will be recorded and reported in the same way as other adverse reactions (see [Section 5](#)).

#### **4.6.2.8. Accountability and unused products**

The antiseptic to be used for the trial will be stored separately from routine supplies in a designated section of the pharmacy, the ward or other appropriate location. The product will be designated for strict use for trial participants. The designated trial pharmacist or midwife will confirm receipt of supplies prior to the commencement of the trial. Inventories will be conducted regularly, and logs returned to the main pharmacy as detailed in the MOP. Inventories will comply with applicable local regulation, GCP and the protocol.

On no account should any product assigned to a participant be used for anyone else. Unused trial product must be returned to the main pharmacy if a participant is withdrawn from treatment before completing their randomised duration of therapy or if there is any remaining product. Procedures for product distribution, labelling, accountability and destruction will be detailed in the Pharmacy MOP. Product accountability will be regularly monitored and the remaining stocks checked against the amounts dispensed. At the end of the trial, all remaining products will be disposed of.

#### **4.6.3. Control group**

Control groups in both strata will receive routine clinical care. The current WHO recommendation during routine vaginal examination is to wash with clean water. Each antiseptic application that occurs will be recorded.

Any topical antiseptic or antimicrobial (all routes) that are used will be recorded on CRFs/worksheets, along with indication for its use.

Both control groups will receive swabs and toxicity assessments as per the schedule (see [Section 4.7](#), [Table 1](#), and [Table 2](#)). The control groups will receive regular assessments, including AE's, the neonates will also receive daily temperature and skin assessments.

